## Abstract

**Background:**

Physical inactivity ranks as a major contributing factor in the development and progression of chronic disease. Lifestyle interventions reduce the progression of chronic disease, however, compliance decreases over time and health effects only persist as long as the new lifestyle is maintained. Telephone counselling (TC) is an effective way to provide individuals with ongoing support to maintain lifestyle changes. Remote physical activity monitoring and feedback (RAMF) via interactive technologies such as activity trackers and smartphones may be a cost-effective alternative to TC, however, this comparison has not been made. This study, therefore, aims to determine the effect of ongoing feedback (TC vs. RAMF) on the maintenance of physical activity following a 12-week individualised lifestyle program, and the effect of this on health risk factors and health services usage.

**Methods and design:**

A randomised controlled trial with a parallel groups design. A total of 150 adults (≥60 years) who participate in a 12-week face-to-face individualised lifestyle program will be randomised to twelve months of RAMF (*n* = 50), TC (*n* = 50), or usual care (*n* = 50). Participants randomised to RAMF will use a smartphone activity tracker app, synced to a wrist worn activity tracker, to provide them with automated feedback regarding compliance to prescribed activity targets. Telephone counselling involves a follow-up phone call every fortnight for the first three months and a monthly call for the remaining nine months of the follow-up period.

The primary outcome measures are physical activity compliance (accelerometry and Active Australia survey). Secondary outcome measures include cardiorespiratory fitness, muscle strength, dynamic balance, quality of life, blood pressure, body composition, and health services usage. Measures will be made before and after the individualised lifestyle program, and at three, six and twelve months during the intervention.

**Discussion:**

The results of this study will help to determine the efficacy of RAMF devices on compliance to prescribed physical activity compared to the current gold standard of TC. If the remote monitoring proves effective, it may provide a cost efficient alternative method of assisting maintenance of behaviour change from lifestyle interventions.

**Trial registration:**

ACTRN12615001104549. Retrospectively Registered 20/10/2015.

## Background

### Ageing and low physical activity levels

There is a substantial body of research which supports the benefits of regular physical activity for health (eg. [1]). Participation in physical activity has been shown to decrease the risk of morbidity and mortality, and loss of independence in older adults and plays an important role in maintaining functional capacity [2]. However, despite the well-known benefits of regular participation in physical activity, physical inactivity in the industrialised world ranks as a major contributing factor in ill-health. Worldwide 31% of the adult population are not meeting the minimum recommendations for physical activity to perpetuate and maintain health in order to prevent disease [3]. Australia’s population over the age of 65 has increased from 1.1 M (9%) in 1973 to 3.3 M (14%) in 2013 [4], and along with this growing population of elderly citizens the number of cases of degenerative and lifestyle diseases has also increased [1]. The highest levels of physical inactivity are also evident in older adults with 18% of Australians aged 40–65 reporting no physical activity [1].

### Benefits of exercise

Strength and/or endurance training activities have been shown to prevent and manage heart failure, diabetes, depression, arthritis and many other conditions that effect older adults [5–7]. However, an issue with much of the existing research is that it has generally involved laboratory-based exercise interventions which have been tightly controlled and attract the most motivated participants. Consequently, while these studies have been helpful in describing many benefits of exercise for a range of chronic conditions, they do not readily translate to interventions that are achievable in clinical practice.

### Lifestyle interventions, issues with ongoing compliance

The use of individualised lifestyle intervention programs may provide a means of addressing the challenges associated with including exercise as a treatment in chronic conditions. Research has reported that lifestyle intervention programs are effective in reducing the progression of chronic disease [8, 9]. While lifestyle interventions are effective in managing chronic disease, there are still issues with ongoing compliance to the altered lifestyle declining over time and health effects only persist as long as the new lifestyle is maintained [10]. Telephone counselling has been shown to be a feasible and cost effective way to provide individuals with ongoing support to maintain lifestyle changes [11, 12]. Review of the literature has shown that interventions lasting greater than 6 months and those with a higher number of calls produce the most favourable outcomes [12].

### Role of new technologies

One method for increasing enjoyment and objectively tracking adherence to exercise programs involves the use of interactive technologies like physical activity trackers. Consumer driven forces for new ways to measure physical activity have led to the development of sophisticated inertial sensing devices for measuring movement of the human body. Until recently, such technology could only be found in expensive and dedicated laboratory facilities.

Devices are now at a price point that it is possible to relatively inexpensively deploy feedback technologies for use in individualized physical activity programs. The use of mobile phones/computers, combined with ubiquitous tracking technologies and management applications, has enabled individuals to better understand their personal health. As smart phones have become more common, two parallel developments have created an easier to use interface than ever before – the large touch screen; and significantly more complex functionality in accelerometers, compasses, GPS and other sensing devices. Additionally, third party creators of specialist sensing devices are now supplying the feedback from these sensors into these smartphones.

Globally, there has been in increase in apps which are designed to improve health through better lifestyle choice, including tracking food intake, tracking activity, encourage healthy food and activity replacements, retaining mental flexibility and support for giving up smoking. Personalised social media-based portals could facilitate motivation for exercise progression through social support [13], including peer- and professional-support [14], and promote health behaviour change [15]. Paired with mobile computing technology, it will be possible to extend current telephone health-coaching concepts to these more automated platforms potentially resulting in greater ongoing compliance to individualized lifestyle programs and resultant improved health outcomes. Emerging technologies which include activity trackers that can provide real time feedback on activity levels and remote social interaction may provide an alternative means of continuing to motivate participants beyond the completion of a formal exercise/lifestyle program. To date however, there is limited research examining the effect of such technologies on the maintenance of activity levels, particularly in older adults.

## Objectives

The study aims to:determine the effect of different modalities of ongoing feedback regarding physical activity on the maintenance of activity levels post completion of a 12-week individualised lifestyle program and;The effect of ongoing physical activity levels on a range of health risk factors and health services usage.

The study will measure and monitor the activity levels of participants during the community based individualised lifestyle program and for 12 months post completion of the program. Participants will be randomly assigned to 1) usual care in the form of physical activity questionnaires plus assessment at 3, 6 and 12 months post program, 2) provided with ongoing feedback through a wrist worn activity tracker and smartphone for the duration of the follow up period and assessment at 3, 6 and 12 months post program or 3) provided with fortnightly to monthly telephone calls for the duration of the follow up period and assessment at 3, 6 and 12 months post program. Follow up assessment at 3, 6 and 12 months will include the collection of physiological variables, functional testing, physical activity and quality of life questionnaires, and health services usage data.

## Methods

### Study protocol

The study involves a parallel group randomised control design to evaluate the potential for activity trackers (Jawbone; Jawbone, Inc. [name]) to be used to provide regular feedback to assist with maintenance of new exercise behaviours following a12-week face to face individualised exercise lifestyle program run by exercise physiologists (Strength2Strength Tasmania Exercise Treatment Initiative). 150 participants who have been referred to the individualised lifestyle program will be recruited for this study. Recruitment will occur through personal invitation at the time of their initial assessment for the lifestyle program. Participants will undergo a suite of tests for variables associated with physical function and clinical prognosis and the beginning and end of the face to face program and at 3, 6 and 12 months of follow-up (Fig. 1). Participants randomised to the activity tracker group will be compared to those who receive usual care and to those who receive telephone counselling, the current best practice for maintenance of lifestyle change.

**Fig. 1 Fig1:**
[figure not shown]
Study Design showing time points for data collection, lifestyle intervention and the three methods of feedback

### Ethical considerations

The study has been approved by the Tasmania Health and Medical Human Research Ethics Committee. Annual progress reports will be made to the ethics committee and they will be notified of any adverse events promptly. The trial has been registered with the Australian New Zealand Clinical trials Registry (ACTRN12615001104549, http://www.anzctr.org.au/default.aspx). Annual progress reports will be provided to the ethics committee and any adverse outcomes will be immediately reported. All data collected will be stored as paper files in a locked filing cabinet and/or electronic files which will be stored on a password protected computer. Only investigators directly associated with the study will have access to these files. Following the completion of the study, participants will have access to their data.

### Selection of participants

Inclusion Criteria are individuals referred to the Strength2Strength (S2S) Tasmania Exercise Treatment Initiative. The S2S Tasmania Exercise Treatment Initiative is an individually tailored 12-week exercise lifestyle program that is led by Accredited Exercise Physiologists and targeted at individuals who are:elderly, frail and agedare at risk of developing chronic diseasehave a chronic medical condition including neurodegenerative disease, cardiovascular disease and conditions, chronic obstructive pulmonary disease (COPD), type 2 diabetes, muscular and/or skeletal conditions, mobility or gait issues and those receiving steroid treatment.

Due to some of the outcome variables from S2S being utilised in the research, participants will be recruited as they commence S2S. The proposed research will investigate the ongoing engagement of S2S participants once they have exited that program. Some of the outcome variables from the S2S program will be utilised in the proposed research but only for those participants who consent to participate in the research study. The reason for use of these outcome variables is to inform of changes in health and physical activity status that occurred during S2S as these changes may impact on how physical activity levels and health outcomes change during the follow up (intervention) period. Data will be collected from S2S site in Launceston, Tasmania, Australia only.

Exclusion criteria: Individuals who choose not to participate in the S2S program will not be considered. Anyone presenting with an unstable medical condition preventing them from participating in regular physical activity; or individuals with neurological conditions, or limited understanding of English which prevent them from meeting the self-reporting requirements of the study will also be excluded.

### Randomisation

Participants who enrol in the study will undergo baseline testing and the 12 week S2S program before being randomised to one of the three intervention groups. Randomisation of participants to intervention groups will be performed at the end of the S2S endpoint testing session. Randomisation will be performed using computer generated blocks of fifteen by a third person not directly involved in the study and will be recorded in sealed opaque envelopes. Each envelope will be opened sequentially at the endpoint S2S endpoint testing session to reveal the allocated intervention. In the event that there are multiple participants from the same household they will be randomised to the same group to maintain the integrity of the intervention. All participants will be requested to avoid the use of any physical monitoring devices other than those directly provided by the researchers for the duration of the study.

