### Telephone counselling

Following the completion of the 12-week Strength2Strength program, participants (*n* = 50) will receive a follow up phone call once a fortnight for the first 3 months of the follow up period, and once a month for the remaining 9 months of the follow up period from the Exercise Physiologists. Participants will be asked to self-report on how they feel they are going with their activity levels and compliance to the home based program and if there are any issues that they feel are preventing them from being more physically active (Fig. 3). Participants will be provided assistance for any specific issues reported. Participants will attend assessments at 3, 6 and 12 months post program completion for collection of physiological variables, functional testing, physical activity and quality of life questionnaires, and health services usage data.

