### Sample size calculation

The 12 week S2S intervention resulted in a mean increase of 450 MET.min of physical activity per week with a SD of 1.5x the change. Sample size was calculated based on a predicted maintenance of 100% of additional physical activity in the feedback groups and decrease of 50% of additional physical activity in the usual care group over the 12-month intervention (Mean Difference = 225 Met.min/week) with a SD of the change of 350 MET.min/week (1.5x the mean change in line with S2S data). STATA 12 (Statistical data analysis; Stata Corp; College Station; Texas, USA) was used to calculate the sample size on the basis of a mean difference of 225 MET.min/week with a SD of the change of 350 MET.min/week, a power of 80% and an alpha level of 0.05 using the “sampsi 0 225, sd (350) p (0.8) a (0.05)” command. The sample size calculation indicated that at least 38 participants were required per group. To allow for potential withdrawals 50 participants per group will be recruited.

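### A single fixed block size of fifteen at one effectively open site lets anyone who keeps a tally know about 9% of allocations in advance; varied, undisclosed blocks or one permuted list would cut that to about 1%

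*Protocol article*

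**What the plan says.** All on this point is in the protocol article.

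- **List.** Randomisation: "Randomisation will be performed using computer generated blocks of fifteen by a third person not directly involved in the study". No other block size, no variation in size and no withholding of the size is described, and the article makes the number public.
- **Concealment.** Allocations "will be recorded in sealed opaque envelopes", and "Each envelope will be opened sequentially at the endpoint S2S endpoint testing session to reveal the allocated intervention". The same section places this after the end-of-program tests and gives members of one household the same arm.
- **Arms and numbers.** Participants complete the 12-week program "before being randomised to one of the three intervention groups". Study protocol: "150 participants who have been referred to the individualised lifestyle program will be recruited for this study". Sample size calculation: "To allow for potential withdrawals 50 participants per group will be recruited".
- **Site.** Selection of participants: "Data will be collected from S2S site in Launceston, Tasmania, Australia only". The same section has participants recruited as they start the program, about 12 weeks before allocation.
- **Visibility of the arms.** One arm is given a wrist-worn tracker, one is telephoned (fortnightly at first, then "once a month for the remaining 9 months of the follow up period from the Exercise Physiologists"), and one receives neither. No blinding of staff or participants is described.

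**The concern.** Sealed opaque envelopes and an independent list-maker protect the content of the next envelope. They do not prevent deduction from envelopes already opened. With one known block size, one sequence and visible arms, a simple tally shows how many places each arm has left in the current block. Once two arms have used their five places, every remaining envelope in that block is certain. Before that point, the arm with most places left is a better-than-chance guess.

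What is at stake is selection and measurement before allocation. Someone who anticipates the next arm could influence the order or timing of endpoint sessions, who goes on to randomisation, or the conduct of the staff-administered end-of-program tests. Any of these could make the arms differ at the point from which maintenance of activity is judged.

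**Working it through.** **The plan's own figure.** The article gives no figure for predictability. Its sample size reproduces: 2 × (1.960 + 0.842)² × (350/225)² = 37.98, so 38 per group, raised to 50 for withdrawals. The present point does not alter it.

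**Inputs.** Block size 15, three arms, 150 participants, 50 per arm (all from the article). Inferred, not stated: 5:5:5 within each block and a constant block size, giving 150/15 = 10 blocks. The observer is assumed to know the block size and every earlier allocation.

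**Certain assignments.** An envelope is certain when only one arm has places left, so the expected number per block is the expected length of the final run of a single arm:

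1 + 4/14 + (4·3)/(14·13) + (4·3·2)/(14·13·12) + (4·3·2·1)/(14·13·12·11) = 15/11 = 1.364.

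That is 1.364/15 = 9.09%, or 13.6 of 150. Simulation gives 9.1%.

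**Guessable assignments.** Always guess the arm with most places left; exact recursion over the remaining counts gives:

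- 7.46 correct per block of 15, i.e. 49.7%, or 74.6 of 150, against 50 of 150 (33.3%) by chance;
- a best guess with probability at least 1/2 for 41.6% of assignments;
- one arm already ruled out for 24.2%, including the certain ones.

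**Would a smaller fixed block help?** No. A known fixed block of 12 gives 11.1% certain, 9 gives 14.3%, 6 gives 20.0% and 3 gives 33.3%. Fifteen is already large for three arms. The weakness is that the size is single and known.

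**Alternatives.**

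| Scheme | Certain | Best guess correct |
|---|---|---|
| Fixed blocks of 15 | 9.1% | 49.7% |
| Sizes varied among 12, 15, 18, 21 | about 1% | about 49% |
| Single permuted list of 150 | about 1% | 39% |

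**Illustrative bias (the steer is an assumption, not from the article).** Suppose participants steered towards a feedback arm and those steered towards usual care differ by 0.25 SD in expected change: 0.25 × 350 = 87.5 MET.min/week. Code the steer as +1 or −1, so that one unit is half the gap, 43.75.

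- *Certain envelopes only.* In each arm 1/11 of assignments are certain. The mean steer is +1/11 in a feedback arm and −1/11 in usual care, a difference of 2/11 = 0.18. Bias = 0.18 × 43.75 ≈ 8 MET.min/week, or 8/225 ≈ 4%.
- *Whenever the best guess is at least 1/2.* The multiplier is 0.364 to 0.40, depending on how ties are handled. Bias = 16 to 18 MET.min/week, or 7% to 8% of 225.

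Both assume that every such envelope is exploited. For scale, the standard error of a difference between two arms of 50 is 350 × √(2/50) = 70 MET.min/week.

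**The case against.** The strongest reply is that the plan already has the main safeguards, and much of it stands. Consent precedes allocation by about 12 weeks, so the usual harm of predictable blocks, choosing whom to enrol, is largely closed. The envelope is opened after the tests, and activity levels are prescribed within the program. The primary measure is a seven-day device recording, which conduct in one session can hardly shape. Reordering sessions would need several participants due at about the same time, some idea of their prognosis and freedom in scheduling; the article documents none of these.

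Several stronger readings are therefore not supported:

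- *That 9% of allocations are in fact known to site staff.* The article does not say who opens the envelopes, who knows the block size, or whether anyone keeps a tally. The figure is what can be known.
- *That the third person has no control over release.* The article is silent on this.
- *That the bias could be 16 to 32 MET.min/week.* That takes ±0.25 SD around the average, a gap of 0.5 SD between steered participants. A gap of 0.25 SD gives half as much.
- *That no analysis could deal with any resulting imbalance.* Changes during the program are collected because they may affect follow-up, so measured imbalance can be seen and adjusted for. Unmeasured imbalance cannot.

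It is also fair to say that varying the block size barely lowers the overall guess rate, and that a single list loses its guaranteed balance if fewer than 150 are randomised. That is a real possibility, since recruitment comes before the 12-week program and allocation after it.

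What the reply does not remove is deduction itself. Opening the envelope after testing does not help if its content was already worked out. The household rule cuts both ways: it disturbs the 5:5:5 counts, but it also makes a later household member's arm known beforehand, so 9% is not an upper limit. The number of such households is not given.

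**Conclusion.** The point holds as a cheap improvement to the design, not as evidence that allocation was compromised. Given 5:5:5 blocks, a constant size and an observer who knows the size and tallies past allocations, about 14 of 150 assignments can be known in advance and about half can be guessed correctly, against a third by chance. The remaining routes to bias are narrow: the order or timing of endpoint sessions, who proceeds to randomisation, and the conduct of staff-administered end-of-program tests. The size of any bias is unknown. The illustration of 8 to 18 MET.min/week rests wholly on an assumed 0.25 SD gap and full exploitation. Even then it is small beside both the 225 planned difference and the standard error of 70.

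**What to change.** For envelopes not yet opened, have the same third person replace the fixed blocks of fifteen with one of the following:

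1. Permuted blocks whose size varies at random among multiples of three (for example 12, 15, 18, 21), with the sizes withheld from site staff. Certain assignments fall from about 9% to about 1%, but the guess rate falls only to about 49%.
2. A single permuted list with no smaller blocks. For a full list of 150, about 1% of assignments are certain and 39% of guesses are correct.

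The second is stronger against guessing; the first is safer for balance if losses before randomisation are expected. The planned sequence of testing first and opening afterwards should stay.

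The cost is a new list and a one-sentence amendment, with no extra staff or participants and no change to the sample size. Balance over calendar time becomes slightly looser: with a largest block of 21, two arms can differ by up to 7 within an unfinished block, against 5 now. With a single list, final arms may be unequal if fewer than 150 are randomised.

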## Data analysis

All statistical analyses will be performed using STATA statistical software (STATA 13; Statistical data analysis; Stata Corp; College Station; Texas, USA). Baseline and descriptive data between the groups will be analysed with one-way ANOVA. Binary categorical data will be analysed for variability between the groups using logistic regression. Parametric longitudinal data will be analysed using mixed effects linear regression with unstructured covariance, corrected for repeated measures. In the event that assumptions of linear regression (heteroskedascity, skewness, kurtosis or non-linearity) are violated, those analyses will be repeated using repeated measures ordinal logistic regression. *P*-Values will be corrected where appropriate for multiple comparisons using the Holm test. Where participants do not return for follow up or there is missing data, this will be analysed on a last case brought forward basis.

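### Household members are allocated as a unit, but the stated analysis and sample size allow for no household correlation, and a member tested later can have a known allocation before the end-of-program test

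*Protocol article*

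**What the plan says.** All of this is in the protocol article.

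- **Allocation rule (Randomisation).** The section provides for "multiple participants from the same household they will be randomised to the same group to maintain the integrity of the intervention".
- **Timing (Randomisation).** "Randomisation of participants to intervention groups will be performed at the end of the S2S endpoint testing session".
- **Concealment (Randomisation).** The sequence is prepared off-study in blocks of fifteen and held in sealed opaque envelopes. "Each envelope will be opened sequentially at the endpoint S2S endpoint testing session to reveal the allocated intervention".
- **Model (Data analysis).** Longitudinal outcomes are analysed by "mixed effects linear regression with unstructured covariance, corrected for repeated measures". The one-way ANOVA, the logistic regression and the ordinal fallback model are also described with no household allowance.
- **Sample size (Sample size calculation).** The number comes from a two-sample Stata command "on the basis of a mean difference of 225 MET.min/week with a SD of the change of 350 MET.min/week", with 80% power and alpha 0.05. It gives 38 per group, raised to 50 for withdrawals. No design effect appears.

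The article does not say how the household rule works when two members reach the end of the program on different days. Nor does it say whether the second member uses up an envelope.

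**The concern.** There are two separate consequences.

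**Precision.** For participants who share a home, the household is what is randomised. Their physical activity is likely to be correlated. The article's own reason for the rule, protecting the integrity of the intervention, accepts that people in one home influence each other. When correlated people always fall in the same arm, the variance of an arm mean is larger than a model for independent individuals reports. Intervals are then too narrow and the test rejects too often.

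**Concealment.** Sealed envelopes protect a participant only while the allocation is unknown. Once the first household member's envelope is opened, the group of the second is settled. If the second member is tested later, that person and the staff can know the arm before the end-of-program measurements. Those measurements are the starting point for a comparison of how well activity is maintained. The later member could also decide whether to go on to randomisation while knowing the arm.

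**Working it through.** **Step 1: reproduce the plan's figure.** Inputs from the Sample size calculation section: difference 225, SD 350 MET.min/week, power 80%, alpha 0.05 (two-sided).

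n per group = 2 × [350 × (1.960 + 0.842) / 225]² = 37.98, so 38. This matches the article, so no allowance for households is built in. The loss allowed for is 1 − 38/50 = 24%.

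**Step 2: variance inflation.** Let s be the share of an arm's participants who are in two-person households and r the within-household ICC. Among n people there are sn/2 pairs, each adding 2rσ² to the variance of the sum. The variance of the arm mean is therefore (σ²/n)(1 + s·r), and the design effect is DE = 1 + s·r.

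- Understatement of the standard error when households are ignored: 1 − 1/√DE.
- True type I error of the uncorrected test: 2 × [1 − Φ(1.960/√DE)].
- Required n: 37.98 × DE, rounded up.
- Power of the corrected test: Φ(225/(SE·√DE) − 1.960), with SE = 350 × √(2/n).

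**Step 3: numbers.** Neither s nor r is in the article, so both are assumptions.

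| s | r | DE | SE understated | Type I error, uncorrected | n needed per group | Corrected power, n = 38 | Corrected power, n = 50 |
|---|---|---|---|---|---|---|---|
| 5% | 0.1 | 1.005 | 0.2% | 5.06% | 39 | 79.8% | 89.4% |
| 10% | 0.3 | 1.030 | 1.5% | 5.35% | 40 | 78.8% | 88.6% |
| 20% | 0.3 | 1.060 | 2.9% | 5.70% | 41 | 77.7% | 87.7% |
| 20% | 0.5 | 1.100 | 4.7% | 6.17% | 42 | 76.2% | 86.5% |
| 30% | 0.5 | 1.150 | 6.7% | 6.76% | 44 | 74.3% | 85.0% |

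**Step 4: keep the two analyses apart.** The type I error column belongs to the analysis as stated. The power columns belong to an analysis that allows for households. At n = 38, SE = 350 × √(2/38) = 80.3 and 225/80.3 = 2.802. The uncorrected test then has power Φ((2.802 − 1.960)/√DE). This is 79.7% at DE 1.03 and 78.4% at DE 1.15. As stated, the analysis therefore loses little power; its fault is the excess of false positives.

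**Step 5: concealment.** No arithmetic applies. Three statements in the Randomisation section are set side by side: household members share a group; each participant is randomised at the end of their own endpoint session; envelopes are opened one after another at those sessions. The Selection of participants section recruits people as they start the program, and nothing requires members of a household to start or finish together. When they finish apart, the first opening fixes the second member's arm before that member's test.

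**The case against.** The strongest reply is that the article is silent on households in the analysis rather than excluding them. A mixed model can take a household term, and an unseen analysis plan may add one. That stands as a limit: a reader might infer that the plan forbids a household adjustment, and the text does not say so. But the article does fix both the allocation rule and the correlation its model handles, and the two do not match as written.

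Second, shared households are mentioned only as a contingency. A reader might infer that type I error is definitely above 5%. The documents do not support that, since it needs shared households to be enrolled and their outcomes to be positively correlated. At the low end of the assumed range the effect is negligible.

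Third, a reader might take a fall in power to 74% as a result of the planned model. It is not. That figure is for the corrected analysis, at the top of the range, with only 38 per group. The plan recruits 50, and it carries earlier values forward for people who do not return instead of dropping them, so 38 analysed is an unfavourable case.

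Fourth, the concealment problem does not arise if members are tested together and the envelope is opened after both have finished. Selective consent is also a narrow risk: people enrol at the start of the program, so it arises only if a second member enrols after the first has been allocated. The primary measure is a seven-day device recording, which limits the scope for influence without removing it. What remains is that the text does not require members to be tested together.

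**Conclusion.** The point holds, at modest size. The allocation unit for shared households is not reflected in the stated model or in the sample size. With positive within-household correlation, standard errors are too small by about 0.2-6.7% and the uncorrected test runs at about 5.1-6.8%. This assumes 5-30% of participants in pairs and an ICC of 0.1-0.5. Corrected power is about 85-89% with 50 per group and about 74-80% with 38 analysed. The trial's power is therefore not in serious doubt on this ground unless losses reach the full allowance and shared households are common.

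The concealment gap is real but conditional. It affects only household members who finish the program at a later session than the first member allocated. A reader should not conclude that concealment fails for participants in general.

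This should be changed because the remedy costs little. It does not undermine the trial.

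**What to change.** **Analysis.** Record a household identifier for every participant. In the between-arm models use household-clustered standard errors, or a household random intercept where there are enough pairs to estimate one. Report how many participants share a household in each arm. The cost is one model option and slightly wider intervals: over the assumed range, wider by a factor of √1.005 to √1.15, or about 0.2-7%. This can be done at any stage if households are recorded.

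**Allocation.** Use one envelope per household and state how it counts within the block of fifteen. Where members finish close together, open it after all currently enrolled members have completed end-of-program testing. Where they do not, take the later member's end-of-program measures with an assessor who does not know the household's allocation. That protects the assessment but cannot stop the participant from knowing, so such cases should be counted and reported. The cost is one line in the envelope procedure and a possible short delay in allocation for some couples. It helps only participants not yet randomised.
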